We will assess the *fidelity* of coordinators to the FCU4Health using an established observation rating system that defines high-quality care and was associated with clinical improvement in studies of the original FCU [53, 54]. A trained coding team will code video or audio recordings of the first FCU4Health feedback session from every family (*N* = 200), and a subset of 80 families will be randomly selected at study entry, balanced by coordinator, for longitudinal coding of all three FCU4Health feedback sessions to assess drift (*N* = 160 additional sessions). In addition, we will develop an automated coding system based on an existing, validated automated coding system for motivational interviewing. Automated fidelity coding will be built from previous methodologies developed for coding fidelity to MI (presence of complex reflections, open-ended questions) [56, 64, 65] and family interventions [66, 67]. Machine-generated fidelity codes have been found to be reliable with human coding across multiple studies [56, 64–66, 68, 69]. Initial algorithm training will use existing FCU feedback session recordings and the FCU fidelity codebook. Automated coding involves a computational “pipeline” of both speech signal processing and machine learning of the audio recordings of the conversations during the sessions, including (1) voice activity detection, (2) diarization (i.e., how many speakers are in session and when is each talking?), (3) role identification (i.e., who is the provider?), (4) automatic speech-to-text transcription, and (5) machine learning models to predict fidelity codes, using lexical (i.e., words) and paralinguistic features as inputs.

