### Data analysis

#### Overview

Analyses focus on implementation data from the families randomized to the FCU4Health. Data from families receiving services as usual will be used in aims 2b and 3. Before data analysis, we will test the psychometric properties (i.e., distribution, reliability) of the measures, conduct a sequence of nested multiple-group confirmatory factor analyses [76] to ensure measurement invariance across language and ethnicity, and apply state-of-the-science data reduction techniques (confirmatory factor analysis, weighted regression scores) by creating multi-indicator, multi-informant construct variables when applicable. These techniques improve measurement properties and result in fewer contrasts, reducing type I error [77]. We expect the attrition rate across waves to be 10–15% based on retention rates for local studies with highly mobile, hard-to-track samples [78, 79]. We will adjust for missing data due to attrition using multiple imputation [80] and full information maximum likelihood [81]. We will perform sensitivity analyses to check the non-response mechanism [82] and attrition analyses to detect differential attrition rates and attrition by group interaction on sociodemographic and pretest variables that may pose a threat to the validity or the equity of the findings [83]. When missingness is not ignorable, we will use complex models to obtain parameter estimates [84]. To estimate power, we used Optimal Design [85] and Monte Carlo simulations in Mplus [84] and referred to relevant publications. All power analyses used 1 − *β* = .80 and *α* = .05 using two-tailed tests. For mediation models, we applied simulation in Mplus for estimating the power of path coefficients and referred to a work by Fritz and MacKinnon [86] for examining significance of mediation effects.

For qualitative data analysis, stakeholder and caregiver interviews and CAB discussions will be audio recorded, transcribed, and then coded using a directed content analysis approach [87] by using existing theory, prior results, and empirical frameworks to develop a coding scheme. Codes will be refined using a subsample of interviews, and then a team of trained coders will code full transcripts. Twenty percent of interviews will be double coded in order to calculate reliability [88]. Disagreements in coding will be resolved via consensus.

#### Aim 1

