#### Aim 2a: fidelity

We will calculate the mean score, interrater correlation coefficient, and internal consistency of the observational ratings. Using a mixed-effects model with random effects for families and a fixed-effects model, we will compare scores from prior FCU trials [53–55, 89] (Smith JD, Dishion TJ, Rudo-Stern J, Stormshak EA, Brown K, Ramos K, Thornton N, Shaw DS, Wilson MN, , A quasi-experimental study of the sensitivity and efficiency of observationally assessing fidelity, submitted) to those from the current trial. We have power to detect a small effect of *d* ≥ .18. Second, we will use the LGC analysis to (1) evaluate drift in fidelity [53] (power to detect a small effect of *d* ≥ .16 for *μ*_slope_) with the sample size of 80 families and 240 feedback sessions and (2) assess the relation between variability in fidelity on program effects (power to detect a small effect of *β* ≥ .10 for *μ*_slope_ on outcomes). To evaluate fidelity using automated coding, we will conduct the same analyses as above but with all 600 feedback sessions. Even when controlling for imperfect reliability, we have power to detect a small effect of *d* ≥ .10 for comparison to previous trials, a small effect of *d* ≥ .11 for *μ*_slope_, and a small effect of *β* ≥ .08 for *μ*_slope_ on outcomes.

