### Study status

At the time this manuscript was submitted for publication, the study was underway. We are planning for our fourth CAB meeting; initial adaptation of the program and assessment is complete; interviewers, coordinators, and other program staff have been trained; and recruitment is in progress at all three agencies. We have also begun formative work on the development of the automated fidelity coding system using data from previous FCU trials.

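### The automated-coding comparison of fidelity with previous FCU trials mixes any true fidelity difference with any shift in how the algorithm scores old and new sessions, and should be calibrated on the 360 human-coded sessions

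*Protocol article*

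**What the plan says.** Four parts of the protocol article bear on this.

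- **The human-coded comparison.** Under Aim 2a: fidelity, observational ratings come first: "we will compare scores from prior FCU trials" with those of the current trial, with a stated detectable effect of d ≥ .18.
- **The automated repeat.** The same section continues: "To evaluate fidelity using automated coding, we will conduct the same analyses as above but with all 600 feedback sessions". It then gives d ≥ .10 "for comparison to previous trials", after an allowance for imperfect reliability. The machine-scored old-versus-new contrast is thus a stated and powered analysis.
- **The training data.** Under Measures, Implementation: "Initial algorithm training will use existing FCU feedback session recordings and the FCU fidelity codebook". Model inputs are words and paralinguistic features. Study status adds: "We have also begun formative work on the development of the automated fidelity coding system using data from previous FCU trials".
- **The content and the human codes.** The Background section on the program says that FCU4Health enlarged the original content toward child and family health behaviors. Under Measures, Implementation, human coders rate the first feedback session of all 200 families. They also rate 160 further sessions from 80 randomly selected families.

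**The concern.** An algorithm that learns from original-FCU sessions may score sessions with added health content systematically higher or lower, even when coordinators are equally faithful. Such a shift coincides exactly with the contrast of interest, previous trials against this trial.

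The article leaves open how the prior sessions are scored, but each possibility carries the problem:

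- **Prior human codes against new machine codes:** two instruments are compared.
- **Prior sessions used in training against new sessions:** fitted scores are compared with out-of-sample predictions.
- **Held-out prior sessions against new sessions:** both are out of sample, but only the new ones carry the altered content.

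At stake is a conclusion that fidelity rose, fell or held steady relative to earlier FCU trials. The automated version looks the more sensitive of the two (.10 against .18). That gain is real only if the offset is zero or has been corrected.

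**Working it through.** **Inputs from the article.** Two-sided α = .05 and power .80 (Data analysis, Overview); 600 automated sessions, that is 200 families × 3; detectable d = .10 (Aim 2a); human-coded sessions 200 + 160 = 360 (Measures, Implementation). Not given: the number of prior sessions, the within-family correlation, and any human–machine agreement figure for FCU4Health sessions.

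**1. The plan's own figure.** With z(.975) + z(.80) = 1.960 + 0.842 = 2.802, the detectable difference is 2.802 × √(1/n_new + 1/n_prior).

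- Best case (prior mean known without error, 600 independent sessions): 2.802/√600 = .114.
- 1,000 prior sessions: .145. 300 prior sessions: .198.

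This simple formula does not reproduce d = .10. A covariate-adjusted or simulated model could give a smaller value, so I do not call the figure wrong. I take it at face value below.

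**2. What a pure scoring offset does.** Let the true fidelity difference be zero and the offset be b (SD units). Then P(reject) = Φ(b/SE − 1.96) + Φ(−b/SE − 1.96). The precision implied by d = .10 is SE = .10/2.802 = .0357. The other two rows assume independent sessions.

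| Precision | SE | b = .05 | b = .10 | b = .20 |
|---|---|---|---|---|
| Implied by d = .10 | .0357 | 29% | 80% | about 100% |
| 600 v 600 (assumed) | .0577 | 14% | 41% | 93% |
| 600 v 300 (assumed) | .0707 | 11% | 29% | 81% |

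The 80% entry is the power definition read the other way: the test cannot tell a .10 SD offset from a .10 SD change in fidelity. More sessions shrink SE and leave b unchanged. A reliability allowance deals with random error and the attenuation it causes, not with an offset.

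**3. Whether the offset can be estimated here.** On double-coded sessions with equal SDs and human–machine correlation r, the paired difference has SD √(2(1 − r)). Its mean over 360 sessions has SE √(2(1 − r))/√360. For an assumed r of .5 to .9, that is .053 to .024, so a mean shift of about .15 to .07 SD is detectable with 80% power. The planned data are enough to see a shift of the size that matters.

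**4. What calibration costs in precision.** All 200 first sessions are human-coded, so for that session number the calibrated mean equals the human mean, with variance 1/200 = .0050. For each of sessions 2 and 3, 80 of 200 are human-coded and the variance is 1/200 + 2(1 − r)(1/80 − 1/200). Weighting the three session numbers equally, and ignoring within-family correlation:

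- r = .5: .0125 each, so (.0050 + 2 × .0125)/9 = .00333, SE .058.
- r = .9: .0065 each, so (.0050 + 2 × .0065)/9 = .00200, SE .045.

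With the prior mean treated as known, the detectable effect becomes 2.802 × .058 = .16 to 2.802 × .045 = .13, against .114 uncalibrated. At r = .5 the result equals that from the human codes alone, (1/200 + 1/80 + 1/80)/9 = .00333. Automated codes therefore add precision to this comparison only when r exceeds .5.

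**The case against.** The strongest reply is that a plausible mechanism is being treated as a fact. Several parts of it stand.

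- Nothing in the article shows that the shift is non-zero, still less that it dominates. The rated dimensions are coordinator skills, the inputs include paralinguistic features, and the core components mirror those of the original FCU, so the shift could be small.
- A reader might infer that the algorithm is trained on the very trials used as comparators. The article mentions existing recordings and previous FCU trials but does not equate them with the comparators.
- Training is called initial, and the system is to be developed and tested within the study. Re-training on FCU4Health sessions is neither stated nor excluded.
- The human-coded comparison is already planned, so a disagreement between the two would be visible.
- Training splits and validation steps are details that an article may leave to the full protocol. Their absence is not the point raised here.
- The reach is limited to one of the three automated analyses in an implementation sub-aim. No primary clinical outcome is touched.

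What the reply does not answer is that the article commits to a powered machine-scored comparison with previous trials and claims better sensitivity for it from more sessions. Under every reading of how prior sessions are scored, a scoring shift would be inseparable from trial in that comparison unless it is corrected.

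**Conclusion.** The point holds in a limited form. The automated comparison with previous FCU trials estimates true fidelity difference plus scoring shift, and the article does not tie it to a correction for the second part. At the stated precision, an offset of .10 SD alone yields a significant result about 80% of the time, or 41% with an assumed 600 independent sessions per side. These rates are conditional on an offset of that size; its actual size is unknown.

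A reader might go further and say that the comparison tests calibration instead of fidelity, or that d ≥ .10 is wrong. The documents support neither: a true difference still contributes to the contrast, and the stated figure cannot be checked without the prior sample size and model. The human-coded comparison (d ≥ .18) and the drift and fidelity–outcome analyses within this trial are not affected by the old-versus-new shift. This is a cheap improvement worth making, not a threat to the trial's main conclusions.

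**What to change.** State that the human-coded comparison is the primary test of fidelity against prior trials. Use automated codes for that comparison only after calibration:

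- Estimate the FCU4Health mean as the automated mean over the 600 sessions plus the mean human-minus-automated difference over the 360 human-coded sessions.
- Weight by session number, because all first sessions but only 80 of each later session are human-coded.
- Use out-of-fold predictions if these sessions also enter training.
- Compare the result with prior-trial human codes, so that both sides are on the human scale.
- Replace d ≥ .10 for this comparison with a figure that includes the calibration variance, the number of prior sessions and the within-family correlation.

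No new data are needed, because the human coding is already planned. The cost is some analysis work and a wider interval: under the assumptions in the working, a best-case detectable effect of about .13 to .16 instead of .114. The automated drift and outcome analyses can stay as they are on this point.

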#### Aim 2b: costs

An ingredient-based cost analysis procedure will be employed to estimate FCU4Health installation and continued implementation costs. Using an activity-based costing approach will allow us to value activities both locally and from national data sources (e.g., US Bureau of Labor Statistics), providing estimates relevant for scale-up in new pediatric care settings nationwide. First, we will conduct a budget impact analysis (BIA) of the cost to install the program (i.e., prior to enrollment and provision of care). BIA provides an estimate of the financial consequences of adopting a new intervention from the perspective of the entity financing the intervention [90]. Second, a multi-perspective cost–benefit analysis will be undertaken to capture the potential impact of the FCU4Health on different key stakeholders (i.e., payor, hospital, family). The fiscal models will be structured to estimate monetary benefits associated with program effects. For significant program effects on the outcome measures in aims 1 and 2, we will calculate the total benefit as a function of the size of the effect (*Q*) and the price per unit (*P*) for each year (*y*). This value can be simply represented as *B*_*y*_ = *Q*_*y*_ × *P*_*y*_. Effects at 6 and 12 months will be adjusted using a discount rate to accommodate the impact of time on our estimates. To avoid overlap or *double-counting* benefits, we will employ a weighted average approach of outcomes [91]. We will calculate the average based on the total effect sizes for each outcome in order to estimate the benefits from a single monetary source. While point estimates often represent the bottom line for such an evaluation (e.g., a return-on-investment amount), a confidence interval that incorporates different values of model input that might feasibly occur is more appropriate given the various model assumptions used [92]. A common model input that could take a range of values represents economic uncertainty (i.e., the discounting rate) [93]. In addition to representing the variation that might be expected due to sampling, we will also consider a range of estimates due to anticipated variation in program characteristics. We will consider how key aspects of the delivery system, such as facility costs or provider salary, might vary with new installations.

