## Methods

### Study aims

#### Aim 1

Aim 1 was to finalize the adaptation of the FCU4Health, which was initially adapted and piloted in pediatric primary healthcare [50], based on input from a community advisory board (CAB) and partner clinics.

#### Aim 2

Aims 2 was to evaluate the effects of two delivery strategies: integrated/co-located care and coordinated care with referral. Using a mixed-methods approach applied to Proctor et al.’s [51, 52] taxonomy, we will evaluate the process of implementing the FCU4Health to inform, taking the program to scale.2a. Evaluate fidelity over time to the FCU4Health using a validated observational rating system [53–55] and develop and test an automated fidelity coding system [56].2b. Employ behavioral intervention costing methods [57] to evaluate the costs of installing and delivering the FCU4Health and conduct a cost–benefit analysis to evaluate the monetary benefits of program effects.2c. Develop a plan to support scale-up and sustainment in collaboration with our CAB.

#### Aim 3

Aim 3 was to use pragmatic trial principles to test program effects on primary and secondary outcomes. Intervention effects on proximal outcomes will be tested as mediators on the distal outcomes of child BMI and body composition.

#### Aim 4

Aim 4 was to carefully track utilization in each aspect of the program, gather data concerning family’s service delivery preferences and satisfaction, and test a model of program implementation where family engagement mediates the relation between fidelity and clinical outcomes [58].

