Results of the adaptation activities are largely descriptive and involve the use of qualitative data from the CAB small group discussions to describe the process and content of adaptations to the program during the course of the trial.

#### Aim 2

In addition to the specific outcomes in aims 2a–2c, we will compare the two arms on stakeholder and caregiver acceptability using repeated-measures analysis of variance (ANOVA) to analyze scores of approximately 30 stakeholders across two time points. We have sufficient power to detect a medium effect for this analysis (*f* ≥ .32). Concerning the variance of caregiver acceptability ratings between groups or over time, we have sufficient power to detect a medium effect (*f* ≥ .28). Latent growth curve (LGC) analyses will be used to determine group differences in the trajectory over time. The estimated power for this analysis is *β* = 0.12.

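### The cost–benefit analysis values an effect only if it is significant, which biases the benefit by selection, and it cites aims 1 and 2 although program effects are tested in Aim 3

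*Protocol article*

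**What the plan says.** Study aims gives sub-aim 2b the task to "conduct a cost–benefit analysis to evaluate the monetary benefits of program effects". The Aim 2b paragraph under Data analysis then states which effects enter, in a sentence that begins "For significant program effects on the outcome measures in aims 1 and 2, we will calculate the total benefit as a function of". The formula is B = Q × P, where Q is the effect and P its unit price, taken year by year. The paragraph gives no rule for an effect that is not significant. Outcomes are afterwards combined by a weighted average to avoid double-counting. The paragraph prefers an interval to a point estimate and lists what will be varied: the discount rate, program characteristics such as facility costs and salaries, and sampling ("In addition to representing the variation that might be expected due to sampling").

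The aims themselves read as follows.

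- Aim 1: "Aim 1 was to finalize the adaptation of the FCU4Health". Its analysis section says "Results of the adaptation activities are largely descriptive".
- Aim 2: "evaluate the effects of two delivery strategies: integrated/co-located care and coordinated care with referral", with sub-aims on fidelity, cost and sustainability.
- Aim 3: "Aim 3 was to use pragmatic trial principles to test program effects on primary and secondary outcomes".
- Aim 4: engagement and participation, including a comparison of participation between conditions.

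The Data analysis overview adds that services-as-usual families contribute data to aims 2b and 3.

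**The concern.** The sentence that defines the benefit points to aims that do not estimate the effect of FCU4Health against control. It therefore does not settle which outcomes are to be monetised.

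The same sentence makes entry into the benefit depend on the p-value. An estimate that crosses the threshold does so partly by chance and tends to exceed the truth. An estimate that misses it has no stated route into the calculation, whether it is favourable or adverse. Both the weighted average and the interval are built on what is left after this step. The same true effect can thus yield an inflated benefit in one realisation of the trial and none in another. At stake is the benefit figure offered from the payor, hospital and family perspectives. The tests on BMI and body composition are not affected.

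**Working it through.** **Aim reference.** Each possible source of Q, set against what the article says it does:

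| Source | Content | Contrast of FCU4Health with services-as-usual? |
|---|---|---|
| Aim 1 | Adaptation, described from qualitative data | No |
| Aim 2, arm comparison | Integrated versus coordinated delivery, acceptability | No |
| Aim 2a | Fidelity; also to "assess the relation between variability in fidelity on program effects" | No, an association with fidelity |
| Aim 2b | Costs and cost–benefit; uses control data | Uses effects; the text does not say it tests them |
| Aim 3 | BMI, body composition, mediators | Yes |
| Aim 4 | Participation between conditions | Yes, for participation only |

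The reference should be to Aim 3, and to Aim 4 if participation is given a monetary value.

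**Inputs for the selection bias.** Two-sided α = .05 and power .80 (Data analysis, Overview); 200 versus 150 families and a detectable d of .25 by ANCOVA (Data analysis, Aim 3); cited BMI effects of d = .20 to .40 across intervention types, and .50 or more for family-centered programs (same section).

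**The plan's own figure.** Without covariates, SE = √(1/200 + 1/150) = .1080, and the detectable effect is 2.8016 × .1080 = .303. ANCOVA multiplies this by √(1 − ρ²), where ρ is the correlation of baseline with outcome. It reaches .25 when ρ = √(1 − (.25/.3026)²) = .56 (about .62 with 10% attrition and .65 with 15%). The article does not give ρ. The figure is attainable, and I take it as the plan's precision:

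SE = .25/2.8016 = .0892.

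The smallest estimate that can be significant is then 1.96 × .0892 = .175.

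**Formula.** For a normal estimate with true value θ, let a = 1.96 − θ/SE. Then, ignoring the negligible lower tail:

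- P(significant) = 1 − Φ(a)
- mean estimate given significance = θ + SE × φ(a)/(1 − Φ(a))
- mean Q if failures count as zero = P(significant) × mean given significance

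For θ = .20: a = 1.96 − 2.2413 = −.281, φ(a) = .3835, 1 − Φ(a) = .6108. The mean given significance is .20 + .0892 × .3835/.6108 = .256, and .6108 × .256 = .156.

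| True d | P(significant) | Mean if significant | Error | Mean Q, failures as zero | Error |
|---|---|---|---|---|---|
| .20 | .61 | .256 | +28% | .156 | −22% |
| .25 | .80 | .281 | +12% | .225 | −10% |
| .30 | .92 | .315 | +5% | .289 | −4% |
| .40 | .99 | .401 | +0.4% | .399 | −0.2% |
| .50 | 1.00 | .500 | 0% | .500 | 0% |

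A simulation of 2,000,000 draws at d = .20, .25 and .40 gives the same values. If every estimate is entered whatever its p-value, expected Q equals the true effect.

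**Range over the unstated correlation.** Error among significant estimates, with SE = .1080 × √(1 − ρ²):

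| Assumed ρ | SE | d = .20 | d = .25 | d = .30 | d = .40 |
|---|---|---|---|---|---|
| 0 | .1080 | +47% | +25% | +13% | +2% |
| .56 (plan's d = .25) | .0892 | +28% | +12% | +5% | +0.4% |
| .7 | .0771 | +17% | +6% | +2% | 0% |
| .8 | .0648 | +8% | +2% | 0% | 0% |

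**The case against.** The strongest reply is that the intent is plain and the damage limited. Sub-aim 2b is about program effects, control families are used for it, and the Aim 2b text refers to effects at 6 and 12 months. A reader might infer from the wrong aim numbers that the analysis has no effectiveness input at all. The documents do not support that: between-condition effects are clearly meant, and this is most likely a numbering slip. The slip still sits in the sentence that defines the benefit.

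The bias also depends on the true effect. If the program achieves the d of .50 or more that the plan cites for family-centered programs, the filter hardly ever acts. That stands. But the plan also cites .20 to .40 and sets its detectable difference at .25, and in the lower part of that range the bias is material.

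Three further inferences go too far.

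- That non-significant effects are set to zero. The article does not say so; it gives no rule. The figures that use zero rest on an assumption.
- That the plan overstates benefit overall. The estimates that pass are too high, but if failures count as zero the average over trials is too low.
- That the interval is simply too narrow. At true d = .20 an ordinary 95% interval around a significant estimate still covers the truth with probability (.975 − .389)/.611 = .96; the fault is mainly in its centre. What can be said is that the promised interval is formed after the selection and does not reflect it.

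Reading significant as substantial does not remove the problem, since that too selects on the observed result.

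**Conclusion.** The point holds in two parts. The reference to aims 1 and 2 does not match the article's numbering and must be corrected. The significance condition is a stated selection rule, not a detail left for a fuller document, and it biases Q.

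At the plan's own precision the effects that are monetised are on average 28% too high at true d = .20, 12% at .25 and about 5% at .30, with nothing of note from .40 upward. On the added assumption that failures count as zero, the expected benefit is 22% too low at .20 and 10% too low at .25. These sizes assume a normally distributed estimate and the standard error implied by d = .25 at 80% power. They grow if baseline adjustment gains less than that and shrink if it gains more. The sampling variation promised for the interval is applied to effects already selected and does not repair this.

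The change should be made, but it concerns a secondary product of the trial and leaves the primary effectiveness analysis untouched.

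**What to change.** In the Aim 2b analysis text:

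1. Replace the reference to aims 1 and 2 with the Aim 3 outcomes, adding Aim 4 participation if it is to be monetised.
2. Name in advance the outcomes to be monetised.
3. Delete the significance condition and enter the point estimate of each named outcome whatever its p-value.
4. Carry the sampling uncertainty of each estimate into the interval for net benefit and return on investment, for example by bootstrap or by draws from its sampling distribution.
5. If a significant-only version is wanted, keep it as a sensitivity analysis.

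This needs no new data. The cost is rewording, a little more analysis and probably a wider interval. The benefit figure may move in either direction.
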